- Normal findings in the medical history, physical and neurological examination, except for dystonia
- Last treatment with botulinum toxin more than two months ago

Exclusion:

- History of seizure disorder
- Pregnancy- a pregnancy test will be performed for women of childbearing potential
- Symptoms of a clinically relevant illness in the 4 weeks before the first study day, including history of any other neurological disorders or conditions requiring the use of anti-depressants that are known to increase seizure threshold, neuroleptic medication, anticholinergic drugs and muscle relaxants with the exception of benzodiazepines
- History of neuroleptic medications/ prior use of neuroleptics
- Presence of pacemaker, implanted medical pump, metal plate or metal object in skull or eye

1. Number of Subjects (Recruitment Target)

Fifteen patients with CD meeting the eligibility requirements will be recruited and enrolled.

1. Recruitment Methods

Patients will be recruited from the Botulinum Toxin Clinic at the University of New Mexico Health Sciences Center, referrals from other neurologists that are sent “Dear Dr.” letters, and word of mouth from participants.

1. Study Timelines

Five study days will be scheduled with the patient. The time between study visits should be no less than 2 days (but can be longer than 2 days if necessary) to allow for “wash-out” of any treatment effects prior to the next intervention. The order of the interventions will be randomized. Subjects will be at least 2 months from previous botulinum toxin injection.

All enrollment activities will be concluded by July 1, 2014 with the analysis to be completed by the end of 2015.

1. Study Endpoints

Primary Study Endpoint

- The study will end once recruitment and completion of all study visits achieved.

Secondary Study Endpoint

- The study would end for an individual participant if they desired to withdraw from the study for any reason. We do not anticipate considerable discomfort to the participant during the study sessions, but if a participant found the experimental procedures intolerable, we would immediately stop the study for that participant.

1. Research Setting

For those participants that require an MRI, they will be scanned at the MIND Research Network. The five intervention appointments will all take place in the Noninvasive Neurostimulation Lab located at the CTSC.

1. Study Methods

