This study is a randomized, sham-controlled, blinded-rater prospective study—based on the methodology of a successful pilot study in patients with blepharospam (Krantz, 2010). Each participant will receive 15-minute sessions of low-frequency (0.2 Hz) rTMS over the primary motor cortex (MC), dorsal premotor cortex (dPM), supplementary motor area (SMA), anterior cingulate cortex (AC), and a sham condition.

The primary outcome measure will be the change in the Toronto Western Spasmodic Torticollis Rating Scale (TWSTRS) score from baseline to after each of the rTMS interventions, including sham.

The patients will be videotaped and we will send the videos to our collaborator, [name] at NIH, for blinded review of the TWSTRS score. The secondary outcome measures include: measurement of a physiologic marker of inhibition (PMI) pre- and post-intervention, subjective patient rating of symptoms, tolerability rating, and a side effect assessment. The rTMS interventions will be guided by a neuronavigation system (Brainsight™) to ensure consistent placement of coil (Figure 2). Brain MRI will be performed on subjects prior to the first study day for registration in the neuronavigation system.

Incentives: Participants will receive incentives on a graduated pay scale: Days 1-3, $20/day and Days 4-5, $40/day for a total of $140/subject who completed all 5 days plus $20/MRI scan time for a total of $160/subject.

Mileage Reimbursement: We will reimburse at the federal rate of $0.565/mile. The head accountant in the Neurology department will register the participants as vendors on Banner (document attached). This method requires obtaining their social security number, but only the accountant will see this information. The forms will be housed in the neurology department and the study coordinator will have no access to them. The "$600 rule" that is often brought up does not apply to mileage reimbursement as it is paying back money and is not perceived as a "benefit" of participating in the study. Therefore, a participant could theoretically be paid out $601+ for mileage and still not be reported to the IRS. There is a "60 day" rule, however. Any money reimbursed 60 days after the study date would be subject to tax. To avoid this issue, a check will be generated every thirty days, when necessary (although most study participants will be completed within 30 days time).

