A paper listing of the link between subject number and identifiable personal information will be kept separate from the main coded dataset and secured in a locked cabinet. This link to the coded information will be kept intact until the end of the study period and in accordance with HRRC and federal requirements for clinical research.

1. List of Appendices

- Dear Dr./Pt letters
- Inclusion/Exclusion Criteria
- Tolerability scoresheet
- Toronto Western Spasmodic Torticollis Rating Scale (TWSTRS)

1. Data and Specimen Banking

- Information and clinical data collected as part of the study will be labeled with participant initials and a study number; information (without the name) will be entered into a computer database/locked file cabinet in the Principal Investigator's office.  The record linking the name to the MRN study ID number (which the MRI scan data is labeled with) will be kept indefinitely at the MRN in a confidential manner in case the participant needs future access to your MRI scan. [name] and her study coordinator will have access to the study information. All other data will be stored for six years and then be destroyed.
- Identification information and data collected from each participant will be entered into the REDCap online data warehouse.
- For each study visit, there will be a neurological exam videotaped both pre- and post-intervention, totaling ten videos. These videos will include identifiable information (i.e. face and voice) and be sent via FedEx 2-day to the NIH collaborator.
- Participation in this study is completely voluntary. Each participant has the right to choose not to participate or to withdraw participation at any point in this study without affecting his/her health care or other services to which they are entitled.

1. Data Management

Data collection and storage

- Information and clinical data collected as part of the study will be labeled with the subject’s initials and a study number, which will be in a locked file cabinet in the locked Principal Investigator’s office; information will also be entered into a secure web-based computer database (REDCap).  The record linking your name to your MRN study ID number (which the MRI scan data is labeled with) will be kept indefinitely at the MRN in a confidential manner in case you need future access to your MRI scan. [name] and her study coordinator will have access to your study information. All other data will be stored for six years and then be destroyed.

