Digital recordings

- To participate in this study, agreeing to release the videos taken of the pre- and post-intervention scales is necessary. For each study visit, there will be a neurological exam videotaped both pre- and post-intervention, totaling ten videos. These videos will include identifiable information (i.e. face and voice).
- The videos will be uploaded to a password-protected computer and then deleted off the camera to ensure safety. For the blinded review, the videos will be burned onto a CD. Each file will be encrypted and must have a password to open. This password will be communicated to the collaborators via phone. The CD will be mailed to [name] using FedEx 2day with a required signature for delivery. The CD will be destroyed within one week of being viewed.

a. The password will be different for each CD.

b. We will communicate the password to the NIH collaborator via phone. The collaborator will write it down and destroy it after viewing the videos and completing the rating scales.

c. 7-Zip is a stronger level of security than Ecommerce uses[1] (i.e. Amazon). It is also universal, so it can be used on a MAC or PC interchangeably.

Statistical Plan

- In this exploratory study, the comparison of the primary outcome measure, the TWSTRS score before and after the interventions, and of the secondary outcome measures will be calculated for each intervention separately. The change in scores will be analyzed using repeated measures ANOVA. Locations will be compared with the Tukey adjustment for multiple comparisons. There are no prior data on the influence of rTMS patients with CD, and hence there is not way to calculate a sample size. We have estimated that 7 patients will give us enough information to find out which intervention over which area exerts the largest influence on cervical dystonia.

1. Provisions to Monitor the Data to Ensure the Safety of Subjects

- This study is not considered greater than minimal risk. The PI confers with her mentors on a regular basis in order to review safety precautions and any questions regarding the protocol.

1. Withdrawal of Subjects

- Any subject is free to withdraw from the study at any time.
- The investigator can remove a participant from the study at any time if she believes that by continuing is not in his/her best medical interest, or if he/she is unable to comply with the requirements of the study.

1. Risks to Subjects

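### Raw change scores in the repeated measures ANOVA are valid but generally less precise than adjusting for the pre-session TWSTRS already recorded at every visit

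*Protocol*

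**What the plan says.** Study Methods defines the primary outcome as the "change in the Toronto Western Spasmodic Torticollis Rating Scale (TWSTRS) score from baseline to after each of the rTMS interventions, including sham". Each participant is to receive four active sites and a sham, and on sequence Study Timelines says: "The order of the interventions will be randomized".

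The Statistical Plan (under Data Management) describes the primary outcome as the score before and after the interventions, to be calculated for each intervention separately. It continues: "The change in scores will be analyzed using repeated measures ANOVA". On the site comparison it adds: "Locations will be compared with the Tukey adjustment for multiple comparisons". It names no baseline covariate.

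The pre-session data exist. Both Data and Specimen Banking and the Digital recordings text say: "For each study visit, there will be a neurological exam videotaped both pre- and post-intervention, totaling ten videos".

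Two further statements bear on size. Number of Subjects sets recruitment at 15, while the Statistical Plan judges 7 patients sufficient. Withdrawal of Subjects says: "Any subject is free to withdraw from the study at any time".

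**The concern.** A change score is the post-session score minus 1 times the pre-session score. That weight is best only if the true within-person slope of post on pre is 1. If the pre-session score varies from visit to visit for reasons that do not carry through fully to the post-session score, subtracting all of it adds noise to every site contrast.

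The aim under Objectives is to pick one premotor target for a Phase II trial, so the precision of the site contrasts decides how useful this small study is. The information needed to estimate the slope is already collected, so any precision lost here could be recovered without burden to participants.

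**Working it through.** **The plan's own figure.** The 7 patients in the Statistical Plan cannot be reproduced. The plan gives no effect size, SD, alpha or power and says that no calculation was possible. The check below therefore compares the variance of two analyses of the same data.

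**Inputs from the protocol.** Five conditions within each participant; randomised order; pre- and post-session scores at each visit; 15 patients (Number of Subjects) or 7 (Statistical Plan).

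**Inputs assumed.** r is the correlation of pre- and post-session score within one session after participant effects are removed (0.3 to 0.9). Pre- and post-session scores have equal within-person variance s². Stable differences in severity between patients do not enter this r.

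**Step 1: variance of a contrast between two sites, per participant.**
- Raw change: 2 × 2s²(1 − r)
- Post-session score adjusted for pre-session score: 2 × s²(1 − r²)
- Ratio, change to adjusted: 2(1 − r)/(1 − r²) = 2/(1 + r)

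| r | change/adjusted variance | adjusted/change variance | SE lower by | 15 adjusted patients are worth, under raw change |
|---|---|---|---|---|
| 0.3 | 1.54 | 0.65 | 19% | 23.1 |
| 0.5 | 1.33 | 0.75 | 13% | 20.0 |
| 0.8 | 1.11 | 0.90 | 5% | 16.7 |
| 0.9 | 1.05 | 0.95 | 2.5% | 15.8 |

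**Step 2: does this survive estimating the slope in a small sample?** The formula treats the slope as known. A simulation estimated it (1,500 runs per setting, participant effects fitted as fixed, no missed sessions) and gave these adjusted/change variance ratios:

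| r | 15 patients | 7 patients |
|---|---|---|
| 0.3 | 0.69 | 0.71 |
| 0.5 | 0.75 | 0.76 |
| 0.8 | 0.91 | 0.96 |
| 0.9 | 0.97 | 1.00 |

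The formula holds well at 15. At 7 with high r the gain all but vanishes. The simulation had no session-number term, so it prices the covariate alone.

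**Step 3: error degrees of freedom, complete data.** The change-score ANOVA has 75 − 15 − 4 = 56 within-person degrees of freedom at 15 patients and 35 − 7 − 4 = 24 at 7. The within-person covariate takes 1 and session number as a factor takes 4, leaving 51 and 19. Entering the participant's mean pre-session score as well costs 1 more, between participants.

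**Step 4: missed sessions (conditional).** If the ANOVA were run in its classical form, only participants with all five sessions would count. If each session is missed independently with probability m, the complete share is (1 − m)^5.
- m = 5%: 0.95^5 = 0.774, or 11.6 of 15
- m = 10%: 0.90^5 = 0.590, or 8.9 of 15

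The protocol gives no miss rate, so m is assumed. Independence is pessimistic: 5% of 75 sessions is about four, and if these fall in one or two people, 14/15 = 93% or 13/15 = 87% are complete.

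**The case against.** The strongest reply is that this is a choice among valid methods. Every participant receives every condition in random order, so a change-score ANOVA is unbiased and conventional for a study that calls itself exploratory. Covariates and estimation detail often belong in a statistical analysis plan, which is not shown. This stands as far as validity goes. It does not remove the point, because the protocol itself fixes change scores as the quantity analysed.

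The second reply is that the gain rests on an r nobody has stated and is only about 5% of the standard error at r = 0.8. That also stands, and it limits the size of the point.

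Some stronger readings are tempting, but the documents do not support them:

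- **That the pre-session scores are wasted.** A visit-specific change score uses them, though with a fixed slope. They would go unused only if one common study baseline were meant, since it cancels from every within-person contrast. The wording of the Statistical Plan and the paired videos at each visit point to the visit's own pre-session score, although Study Methods says only baseline.
- **That incomplete participants will be dropped.** This belongs to the classical procedure. The protocol does not prescribe it, and a repeated measures ANOVA can be fitted as a mixed model on all sessions. Visits may also be spaced further apart, so a missed appointment need not be a lost session.
- **That the plan is faulty for assuming equal variances of pairwise differences.** The protocol does not state a pooled error, and a mixed model with only a random participant effect makes the same assumption, so this is no reason to switch.
- **That this choice costs more than any other in the analysis.** Nothing in the documents allows that comparison.

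**Conclusion.** The point holds as one of efficiency. Fixing the slope at 1 is valid but generally less precise than adjusting for the pre-session score, with a variance ratio of 2/(1 + r): 1.33 at r = 0.5, 1.11 at r = 0.8 and 1.05 at r = 0.9. This rests on equal pre- and post-session variance within person and on an assumed r. With 15 patients the gain is worthwhile at moderate r and small at high r; with 7 patients and r near 0.9 there is none to see. The conflict between 15 and 7 is a separate matter that must be reconciled, but it decides which of these cases applies.

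Using all completed sessions guards against a further loss that would arise only if a complete-case ANOVA were run. That benefit comes from keeping the sessions and would also be had from a change-score model fitted to all of them. The change is worth making because it is nearly free. A reader should not conclude that the planned analysis would mislead.

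**What to change.** In the Statistical Plan, make the primary analysis a linear mixed model of post-session TWSTRS with:

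- condition and session number as fixed effects, and participant as a random effect;
- that visit's pre-session score as covariate, split into the participant's mean and the visit's deviation from it, so that differences in severity between patients do not distort the within-person slope;
- all completed sessions, Kenward-Roger degrees of freedom, and Tukey-adjusted site comparisons as now planned.

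In Study Methods, state that baseline means the same visit's pre-session score. Keep the change-score repeated measures ANOVA as a sensitivity analysis.

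The cost is a few lines of protocol text, slightly more analysis work and about 5 to 6 degrees of freedom (1 to 2 for the covariate, 4 for session number as a factor). That is minor at 15 patients and more noticeable at 7. No new data are needed.

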This is a well-known location for MRI research with easy parking and appropriate study staff in place.

1. Prior Approvals/Attachments Requiring Signatures

N/A

1. Confidentiality

The screening for ineligible candidates will be destroyed after the project's completion (12 months). The document containing contact/personal information for enrolled participants will be kept on a password-protected computer

It is imperative that video be taken for further analysis of therapeutic benefit after each of the 5 visit procedures. [name] will also be performing a blinded review of the videos to confirm rating scale analysis.

Direct identifiers such as name, address and telephone number will be maintained in the event that subjects need to be re-contacted during the study duration due to re-consent or other event. The need to re-consent could occur if new information about safety parameters was learned during the duration of the study in a password-protected computer in the locked office of the principal investigator and kept for for six years under the HIPAA protocol.

The clinical data will be stripped of all identifying information, but the videos will contain head shots of the participants. This detail will be thoroughly covered during the consent process.

Additional details on confidentiality have been covered in Sections 13 and 14.

1. Provisions to Protect the Privacy of Subjects

All research appointments are conducted in the PI’s Noninvasive Neurostimulation Lab on the 2nd floor of the CTSC. The door is kept closed during experiment appointments.

1. Compensation for Research-Related Injury

If a participant is injured or becomes sick as a result of this study, UNMHSC will provide with emergency treatment, at the participant’s cost. No commitment is made by the University of New Mexico Health Sciences Center (UNMHSC) or MRN to provide free medical care or money for injuries to participants in this study.

In the event that a participant has an injury or illness that is caused by participation in this study, reimbursement for all related costs of care will be sought from the participant’s insurer, managed care plan, or other benefits program. If he/she do not have insurance, the participant may be responsible for these costs. He/she will also be responsible for any associated co-payments or deductibles required by the insurance company.

**HIPAA Authorization**

- Identifiers include videotaping the participants, which includes full-face coverage.
- Please see accepted HIPAA in CLICK.

**Non-English Speaking Subjects**

- No non-English speaking subjects are being recruited for this study.

**Planned Emergency Research Consents**

- N/A

**Cognitively Impaired Adults/ Adults Unable to Consent/ Use of a Legally Authorized Representative (LAR)**

- N/A

1. Drugs or Devices

**Medical Devices: Please respond to all questions in this section.**

A Magstim Rapid2 rTMS device and a Magstim BiStim paired-pulse TMS device are used in the study (The Magstim Company Limited, [name]). The rTMS device is used to enhance inhibition over various areas in the premotor and motor cortex in order to improve symptoms of cervical dystonia.

Has an Investigational Device Exemption (IDE) application been submitted to the FDA?

No.

The device meets the requirements for an abbreviated IDE if all of the following are TRUE. Please articulate responses to all of the following:

- The device is not banned. **TRUE.** rTMS is FDA-approved for the treatment of treatment-resistant depression. In addition, TMS has been FDA-approved for the treatment of migraine.
- The device is not a significant risk device. **TRUE.** The UNM HRRC determined that the TMS devices are not significant risk devices according to this protocol.
- The sponsor or investigator will label the device in accordance with 21CFR812.5. **TRUE.** The devices are labeled accordingly.
- The sponsor or investigator will comply with the requirements of 21CFR812.46 with respect to monitoring investigations. **TRUE.** The investigator will comply with the requirements regarding monitoring of investigations.
- The sponsor or investigator will maintain research records required under 21CFR812.140 (b) and (5) and make the reports required under 21CFR812.150 (b) (1) through (3) and (5) through (10). **TRUE.** The investigator will maintain research records as described.
- The sponsor or investigator will ensure that participating investigators maintain the records required by 21CFR812.140 (a)(3)(i) and make the reports required under 21CFR812.150(a) (1) (2) (5) and (7). **TRUE.** The investigator will ensure that all study staff and investigators maintain records as described above.
- The sponsor or investigator will comply with the prohibitions in 21CFR812.7 against promotion and other practices. **TRUE.** The investigator will comply with all prohibitions against promotion and other practices.

Please complete the section below to determine if an IDE is required:

- Is the device FDA-approved for marketing and is it being used or investigated in accordance with its labeling.
  - **Yes.** rTMS and recently TMS are approved by the FDA for treatment of depression and migraine. Our proposal uses an even lower stimulation rate, suggesting continued use within clearly safe parameters.
- Is the device a diagnostic device?
  - No.
- Is the device undergoing consumer preference testing, testing of a modification, or testing of a combination of two or more devices in commercial distribution?
  - No.
- Is the device testing for the purpose of determining safety and effectiveness?
  - **Yes.** We are testing the effectiveness of rTMS in treatment of cervical dystonia symptoms.
- Is the device a custom device as defined in 21CFR812.3(b)?
  - No.

Provide a detailed description of device storage and accountability procedures:

- Where will the device be shipped within UNM?
  - The device is already housed at UNM in the Noninvasive Neurostimulation Lab.
- Where will the device be stored?
  - The device is stored in the locked Noninvasive Neurostimulation Lab at UNM on the 2nd Floor of the CTSC.
- Who will have access to the device?
  - The access to the device will be limited to the PI who is fellowship trained in operating these devices and to the study personnel who are trained to use the devices safely.
- What security safeguards are in place to ensure proper accountability, access and storage of the device?
  - The devices are stored with the locked Noninvasive Neurostimulation Lab. The PI assumes accountability for the devices and their proper use.
- If the device is experimental, will it be labeled “Investigational Use Only”?
  - Yes.
- Who will be responsible for:
  - Device accountability. The PI.
  - Labeling/ dispensing. The PI.
  - State the qualifications of this person. The PI is fellowship trained in Human Motor Control and trained to use TMS devices. She has published in the areas of TMS and rTMS.

Describe how the investigational device is controlled, and how accidental use outside of approved research will be avoided.

The investigational device has two switches that must be pressed in sequence in order to turn on the device. The device is activated through computer control, which must be accessed through a password-protected computer and knowledge of the Signal software program. Finally, the handheld coils will not discharge unless 2 buttons on either side of the coil are held down simultaneously. The multistep procedure would ensure that an untrained person would be very unlikely to know how to operate the entire setup to cause discharge of the TMS. Again, the device is within a locked laboratory.

Non-Significant Risk Determination Section

- Is the device intended as an implant (≥30 days)?
  - No.
- Is the device for use supporting or sustaining human life?
  - No.
- Is the device for a use of substantial importance in diagnosing, curing, mitigating or treating disease or preventing impairment of human health?
  - No. This protocol is an exploratory study to determine whether rTMS has a beneficial effect on dystonia symptoms to provide preliminary data for a definitive clinical trial.
- Does the use of the device present a potential for serious risk to health, safety or welfare of the subjects?
  - The use of the device does not pose the potential for serious risk to health, safety or welfare of subjects. The protocol parameters are well within the bounds determined by the FDA for approval for the treatment of depression and migraine.

Explain why the use of the device in this study poses non-significant risk, and attach any other supporting information. In addition, explain whether the sponsor, the FDA or any other oversight organization has already made a risk determination for the device.

The device poses a non-significant risk to participants given that the parameters used are well within the FDA-approved rTMS therapy for the treatment of depression. The exclusion and inclusion criteria also ensure an added level of safety in using this device.
